### Recruitment {15}

Prospectively participants diagnosed with RR-TB are enrolled by RR-TB clinic staff in inpatient or outpatient facilities.

## Assignment of interventions: allocation

### Sequence generation {16a}

We randomise by monthly blocks. Depending of the month in which patients are diagnosed with RR-TB, patients with FQ-susceptible RR-TB are enrolled in either the experimental arm (WHO all-oral regimen, with BDQ and LZD) or control arm (STR that contains either a SLID or LZD) regimen. A coin toss determined which treatment arm is used for even (February, April, ...) or odd (January, March, ...) months for all RR-TB Units. The coin toss determined that odd months correspond to the experimental arm and even months to the control arm. The coin toss was done on 09 April 2021 by the principal investigator in the presence of the director of the NTP and all RR-TB units researchers to ensure that patients in the same clinic are treated with both the intervention during the trial study period. Following the coin toss, patients diagnosed in odd months are enrolled in the experimental arm, and those diagnosed in even months in the control arm (Fig. 1).

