Considering the highly effective RR-TB treatment strategy used in Niger, it was not justified to introduce the WHO BDQ/LZD-containing STR without a rigorous evaluation. We therefore aim to compare the safety, effectiveness and adherence of the WHO all-oral BDQ/LZD-containing STR (experimental arm) with the Niger RR-TB treatment strategy, using a SLID-containing regimen, with LZD replacing the SLID in case of ototoxicity (control arm). To provide high-level evidence on the one hand, but also timely inform local and international guidelines, we used an approach that would be feasible for the local RR-TB programme. We designed a pragmatic randomised clinical trial with stratified block randomisation, using the month of RR-TB diagnosis as stratifying variable. The study protocol is presented here.

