### Eligibility criteria {10}

Patients are eligible for the study if all of the following conditions are met: (1) have bacteriologically confirmed TB with evidence of resistance to rifampicin (for children the diagnosis is not always bacteriologically confirmed as the RR-TB diagnosis may be based on clinical TB diagnosis plus history of a close contact with a confirmed RR-TB case) and susceptibility to fluoroquinolones and (2) be willing and able to give informed consent to participate in the study (signed or witnessed consent if the patient is illiterate; signed or witnessed consent by a child’s parent or legal guardian).

Exclusion criteria: a patient is ineligible for the study if any of the following conditions are present: (1) previous treatment for more than one month with second-line TB drugs included in the treatment regimens to be evaluated (disregard E and Z, which may have been used previously in first-line treatment), (2) a health rate-corrected QT (QTc) interval ≥ 500 msec at baseline that is not corrected by medical management, (3) any other medical contraindications for taking the study regimens, (4) being younger than 6 years old, and (5) diabetes mellitus.

As during routine practice, pregnant women are not excluded from treatment and thus not from the study. The patient information sheet states that there is a lack of safety data during pregnancy.

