## Assignment of interventions: blinding

### Concealment mechanism and implementation; blinding {16b} {16c}{17a} {17b}

Laboratory staff who perform testing for the diagnosis of RR-TB are blinded to treatment assignment. They do not know which regimen is allocated to a given month. However, the RR-TB clinicians, patients (placebo is not feasible for TB regimens combining up to seven drugs, of which one is an injectable in one arm), and the researcher and statistician are not blinded for the regimens. When the patient arrives at the RR-TB clinic, depending of the month of RR-TB diagnosis the patient is either assigned to the experimental or control arm by the RR-TB clinic staff.

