## Discussion

In Niger, during the past 10 years, the RR-TB treatment strategy was highly successful, with 83% relapse-free cure [8]. RR-TB patients are treated with a SLID-containing STR. The STR’s SLID is replaced by LZD in patients with ototoxicity. Audiometry is done at baseline and on a monthly basis during treatment. As any audiometry abnormality serves as indication for switching to LZD, not a single RR-TB patient developed severe hearing loss since 2017 [15]. BDQ is safeguarded for the rare patients with treatment failure or relapse after a first STR, leaving not a single patient without a treatment option [8]. Since 2020 WHO recommends constituting all-oral STR, thus replacing the SLID with bedaquiline. Considering the highly successful Niger RR-TB treatment strategy, it could only be modified if a rigorous evaluation, relying on the unbiased comparison between the all-oral WHO STR and the Niger RR-TB treatment approach would show benefits in terms of safety and effectiveness.

To maximally avoid bias, patients had to be randomly assigned to either an experimental arm, using the all-oral WHO STR, or the control arm, relying on the Niger RR-TB treatment approach. To increase the feasibility of conducting a RCT, embedded in routine activities of all four RR-TB clinics in Niger, we adapted our trial design. First, instead of randomising patients on an individual basis to either the newly recommended all-oral WHO STR or the control arm, relying on the SLID-containing STR for most and with LZD replacing the SLID in case of any ototoxicity, we randomised by monthly blocks, whereby the regimen used changes every month. This approach simplifies the work of the clinicians running the RR-TB clinics and also overseeing this trial. With monthly blocks, major causes of bias are prevented as patients are not assigned by the clinician to one or another treatment arm. Allocation to a month is defined by the date of RR-TB diagnosis, which seems a better option than the date of RR-TB treatment start, as treatment start could be delayed by the clinician depending on how he perceives both regimens.

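### The allocation is odd/even-month alternation after one coin toss, not stratified block randomisation, and staff who screen and enrol patients can know the arm beforehand

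*Protocol article*

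**What the plan says.** The Abstract, Background and rationale {6a} and Trial design {8} all name the design stratified block randomisation. The Background gives the form: "stratified block randomisation, using the month of RR-TB diagnosis as stratifying variable".

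Sequence generation {16a} sets out the mechanism. One coin was tossed on 9 April 2021, by the principal investigator in front of the researchers from all units. The result was that "The coin toss determined that odd months correspond to the experimental arm and even months to the control arm". From then on, "patients diagnosed in odd months are enrolled in the experimental arm, and those diagnosed in even months in the control arm". Trial status dates the start of recruitment at all four sites to 15 April 2021.

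On concealment and blinding ({16b} to {17b}), laboratory staff are said not to know which regimen belongs to which month. Clinicians, patients, the researcher and the statistician are not blinded. At the clinic, "depending of the month of RR-TB diagnosis the patient is either assigned to the experimental or control arm by the RR-TB clinic staff". The consent section {26a} and Recruitment {15} give informing and enrolling patients to the same clinic staff. Eligibility criteria {10} include a judgement item: "any other medical contraindications for taking the study regimens".

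The Discussion states that "With monthly blocks, major causes of bias are prevented as patients are not assigned by the clinician to one or another treatment arm". It also expects random allocation by month to overcome confounding, and later concedes that monthly allocation is more open to confounding than individual randomisation.

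**The concern.** Two things are at issue. The first is the label. In stratified block randomisation, patients (or clusters) are randomly ordered within blocks inside each stratum. Here nothing is random within a month, and no month is random once the toss is done. A reader who trusts the label will credit the trial with protection that it does not have.

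The second is foreknowledge. Anyone holding the diagnosis date and knowing the odd/even rule knows the arm before eligibility and consent are settled. The regimens differ in their drugs and monitoring, the investigators state a prior expectation that the experimental arm is less safe, and one exclusion is a matter of judgement. Patients judged ineligible or refusing leave the trial, and the primary analysis includes only those who started treatment, so it cannot bring them back. The primary endpoint is uncommon, so a few selectively omitted high-risk patients could shift the comparison and the interim stopping decisions that rest on it.

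**Working it through.** **1. How much of the allocation is random.** Inputs: one toss ({16a}); recruitment from 15 April 2021 to 14 April 2024 (Trial status). The window touches 37 calendar months: 18 odd and 19 even, counting two part-Aprils, or 552 odd-month days and 544 even-month days. One toss leaves 2 possible sequences over all 37 months. After 9 April 2021 each month's arm is fully determined. Participant timeline {13} could be read as one toss per month; {16a} rules that out.

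**2. Who knows the arm, and when.** The sections side by side:
- Date of diagnosis: set by laboratory staff stated to be unaware of the month-regimen link.
- Eligibility, information and enrolment: clinic staff, unblinded ({26a}, {15}, {17a}).
- Assignment: the same clinic staff, from the month of diagnosis ({16b}, {16c}).
- Table 1 lists screening and consent above allocation, but all three fall in one enrolment column, and the printed diagnosis date already discloses the arm.

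The two stated safeguards, laboratory blinding and use of the diagnosis date rather than the treatment start date, limit steering of the date. Neither reaches the eligibility and consent step.

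**3. The plan's own figure.** The sample size does not cause the problem. With hazard ratio 3.2, two-sided alpha 0.05 and power 0.8, the Schoenfeld formula gives (1.960 + 0.842)² / (0.25 × (ln 3.2)²) = 23.2 events. Divided by the mean event rate, (5% + 15%)/2 = 10%, this is 232 patients, close to the stated 230. Expected patients with an event are 115 × 5% = 5.75 and 115 × 15% = 17.25, so the comparison rests on about 6 against 17.

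**4. What selection could do (assumed figures, none from the document).** Suppose 20% of patients have three times the risk of the rest, and a share q of them is left out in one arm's months only. With mean risk p, the lower risk is r = p / (0.8 + 0.2 × 3) = p / 1.4. The rate among those enrolled is r × (0.8 + 0.6(1 − q)) / (0.8 + 0.2(1 − q)).

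| q | Left out in experimental months: rates (ratio) | Left out in control months: rates (ratio) |
|---|---|---|
| 0 | 15.0% v 5.0% (3.0) | 15.0% v 5.0% (3.0) |
| 25% | 14.1% v 5.0% (2.8) | 15.0% v 4.7% (3.2) |
| 50% | 13.1% v 5.0% (2.6) | 15.0% v 4.4% (3.4) |
| 100% | 10.7% v 5.0% (2.1) | 15.0% v 3.6% (4.2) |

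The same factors apply if the drugs do not differ: a true ratio of 1 would appear as 0.94, 0.87 or 0.71 with omission in experimental months, and as 1.06, 1.15 or 1.40 with omission in control months. The last row is an extreme.

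**The case against.** The strongest defence has four parts.

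First, the alternation is openly described, its feasibility is argued, and the Discussion admits vulnerability to confounding and plans multivariable adjustment. That stands as disclosure of confounding. It does not name selection from foreknowledge, and adjustment for measured factors cannot remove selection on unmeasured ones.

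Second, the exclusion refers to the study regimens in the plural, so it can be read as requiring fitness for both regimens in every month. On that reading, arm-specific exclusion would be a misapplication of the rule, not something the rule allows. This stands: the protocol does not license selective exclusion. But nothing in the article says that the criterion is applied identically in odd and even months.

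Third, laboratory blinding and the diagnosis-date rule are real safeguards. They stand for the date and stop short of screening and consent.

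Fourth, selection would be detectable. The registration rate is defined under {18a}, and Data management {19} names laboratory and treatment registers, so confirmed and started patients can be counted by month. This also stands, so a reader should not infer that selective enrolment would be invisible. The registration rate is simply not planned by arm.

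A reader might further argue that with two possible sequences no p-value below 0.5 is attainable. That floor belongs to a design-based randomisation test. The plan uses chi-square and Cox regression, so the floor does not measure the error of the planned analysis.

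**Conclusion.** The point holds in two parts. The design label is wrong as written: this is alternation by month of diagnosis after one coin toss, with month as the allocation rule. And the arm is not concealed from those who judge eligibility, inform patients and assign treatment, so selective exclusion or refusal by arm is possible. The Discussion's statement that major causes of bias are prevented therefore goes further than the mechanism supports. Its stated reason, that the clinician does not assign, also sits badly with assignment by clinic staff under {16b} and {16c}; the fair reading is that staff apply a fixed rule, which they know.

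The documents do not show that bias has occurred, and neither its size nor its direction can be derived from them. The risk ratios from 2.1 to 4.2 around a true 3.0 rest wholly on the assumed 20% prevalence, threefold risk and one-sided omission.

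A reader might also infer that the month order must be re-drawn at random mid-trial. That does not follow: with one regimen per month, staff would still know the current month's arm, so re-drawing would not conceal it at screening.

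**What to change.** 1. In the Abstract, {6a}, {8}, {16a} and the Discussion, describe the allocation as alternation by calendar month of diagnosis after a single coin toss, without concealment from enrolling staff. Withdraw the statements that major causes of bias are prevented and that random allocation overcomes confounding. Name selection from foreknowledge among the weaknesses.
2. For every confirmed RR-TB patient from now on, in odd and even months alike, record eligibility against both regimens. State that the exclusion for contraindications to the study regimens is applied identically in both arms.
3. Report by arm month the registration rate, exclusions with reasons, refusals and baseline characteristics, using the existing laboratory and treatment registers. The counts of confirmed and started patients should be recoverable for those already enrolled; whether reasons for exclusion and refusals were recorded is not stated, and any gap should be reported.

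The cost is a short screening log, an amendment to the ethics bodies if the log counts as a procedural change under {25}, and a less favourable description of the design. Clinics keep one regimen per month. If enrolment has closed, items 1 and 3 can still be done.

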**Fig. 1 Fig1:**
[figure not shown]
Flowchart showing study enrolment. # In addition to the prospective arms, a retrospective cohort of 255 patients enrolled on treatment between 2017 and April 2021 will be used during an interim analysis [if characteristics known to affect treatment outcome of the retrospective cohort are not significantly different from the prospective arms, and in case the proportion with a grade 3–5 adverse event is not significantly different between the retrospective cohort and those prospectively treated using the Niger RR-TB treatment strategy (SLID-containing regimen, with LZD replacing the SLID in case of ototoxicity)]

Data collected from patients who started RR-TB treatment between 1 January 2017 and 15 April 2021, when trial enrolment started, will be used for an interim analysis.

## Assignment of interventions: blinding

### Concealment mechanism and implementation; blinding {16b} {16c}{17a} {17b}

Laboratory staff who perform testing for the diagnosis of RR-TB are blinded to treatment assignment. They do not know which regimen is allocated to a given month. However, the RR-TB clinicians, patients (placebo is not feasible for TB regimens combining up to seven drugs, of which one is an injectable in one arm), and the researcher and statistician are not blinded for the regimens. When the patient arrives at the RR-TB clinic, depending of the month of RR-TB diagnosis the patient is either assigned to the experimental or control arm by the RR-TB clinic staff.

## Data collection and management

### Plans for assessment and collection of outcomes {18a}

Safety: Patients will be screened monthly by a person trained in the diagnosis and management of AE.

During the inclusion visit, pathologies associated with a high risk of adverse effects such as diabetes, kidney and liver failure, malnutrition, HIV infection, alcohol and drug abuse, etc. should be identified and recorded. The underlying causes of adverse effects will be identified and treated.

AE are classified according to their severity using ARNS scale (Table 2) and noted in the patient’s file.

**Table 2 Tab2:** Severity rating of adverse effects

Degree	Description
Degree 1: Slight abnormality	Mild or transient discomfort, without limitation of usual daily activity; does not require medical intervention or corrective treatment.
Grade 2: Moderate abnormality	Partial limitation of usual daily activity; medical intervention or corrective treatment required. No need to interrupt treatment.
Grade 3: Severe abnormality	Limitation of usual daily activity; requires medical intervention and corrective treatment, possible hospitalisation. It may be necessary to stop the responsible medication temporarily until the symptoms disappear.
Grade 4: Life threatening or permanent injury	Very limited activity; requiring medical intervention and corrective treatment, almost always in a hospital environment. It may be necessary to stop the responsible drug permanently.
Grade 5: Death	

Grade 1 adverse events will only be recorded in the patient's file without further action; those of grade 2 often require a medical intervention with auxiliary drugs

Any grade 3–5 AE are classified as severe AE

All AE will be reported in the patient treatment card. When an AE occurs, the investigator responsible for the care of the patient will first assess and grade the event. If it is graded 4–5, or if other serious AE (SAE) criteria (such as hospitalisation) apply, then a “severe AE form” will be completed and sent to the principal investigator and the relevant pharmacovigilance authority (Fig.1).

The relationship between a severe AE and drugs used in the STR can only be carried out by the physician in charge of the study. He will analyse and consider possible other causes of the observed AE before concluding that they are due to a particular anti-TB drug. The categories showing the level of causality categories include “definite,” “probable,” “possible,” “unlikely,” “not related,” and “unclassifiable” and are detailed in Table 3.

**Table 3 Tab3:** Scale for attribution of assessing drug relationship with AE occurrence

Category	Definition
Definite	Events occurring within a timely manner after administration of the drug(s); that are known sequela to the administration of the drug(s) and follow a previously documented pattern of reaction, but for which no other explanation is known. This category applies to AEs that the principal investigator believes are incontrovertibly related to the treatment.
Probable	Any event occurring in a timely manner after administration of the drug(s); that follows a known pattern of reaction to the drug(s); and for which no other explanation is known. This category applies to AEs that, after careful medical consideration at the time they are evaluated, are believed with a high degree of certainty to be related to the drug(s).
Possible	Any event occurring in a timely manner after administration of the drug(s) that does not follow a known pattern of reaction and for which no other explanation is known. This category applies to AEs that, after careful medical consideration at the time they are evaluated, are considered unlikely to be related but that cannot be ruled out with certainty.
Unlikely	In general, this category can be considered applicable to those AEs that, after careful medical consideration at the time they are evaluated, are considered to be unrelated to administration of the drug(s).
Not related	Any AEs for which there is evidence that an alternative aetiology exists or for which no timely relationship exists to the administration of the drug(s) and the AEs do not follow any previously documented pattern. This category applies to those AEs that, after careful medical consideration, are clearly and incontrovertibly due to causes other than the drug(s).
unclassifiable (insufficient data to assess)	There is insufficient information about the AE to allow for an assessment of causality.

Effectiveness: Outcomes will be assessed during treatment and, in case of cure or treatment completion, at the end of 12 months post-treatment follow-up

*Therapeutic success*: Composite result corresponding to the combination of “cured” + “treatment completed” (= treatment success) without relapse during the 12-month follow-up period

Note: this result can also be defined as “recovery without relapse”.

*Cured*: A patient with bacteriologically confirmed RR-TB who has completed 9-11 months of treatment without evidence of treatment failure AND at least 2 consecutive cultures at least 30 days apart are negative in the continuation phase and not followed by a positive culture result during treatment and post-treatment follow-up.

*Treatment completed*: A patient who has completed 9 to 11 months of treatment with the regimen with no evidence of treatment failure BUT not fulfilling the definition of “cured”.

*Treatment failure*: The treatment is interrupted or it is necessary to permanently change the treatment regimen of at least two anti-tuberculosis drugs due to:A lack of bacteriological conversion of sputum after 6 months of treatment, orA reversion of the sputum bacteriological culture after 7 months of treatment in a patient with a previously negative culture, orEvidence of additional drug resistance acquired in the treatment regimen of the study in patients with either treatment failure or relapse, and without proof of a between baseline and recurrence genotypically different strain, orAE leading to the modification of at least two anti-TB drugs in the treatment regimen

*Deceased*: A patient who has died during treatment from any cause.

*Lost to follow-up:* A patient whose treatment has been interrupted for 2 or more consecutive months.

*Not evaluated*: A patient for whom no treatment outcome is assigned (this includes cases “transferred out of the study area” to another treatment unit and whose treatment outcome is unknown or cannot be assessed)

*Relapse:* A patient who has been treated for RR-TB, has been declared “cured” or “treatment completed” and is diagnosed with another episode of confirmed RR-TB with rifampicin-resistant bacilli, within one-year follow-up, and without proof of a between baseline and recurrence genotypically different strain.

*Reinfection:* Recurrence (treatment failure or relapse) with proof of a between baseline and recurrence genotypically different strain.

*Withdrawn*: A patient is withdrawn from treatment for a reason other than treatment failure (e.g. resistance to second-line basic drugs, the patient’s informed consent is withdrawn or other reasons) and referred back to the standard treatment programme for routine care.

For the purpose of the effectiveness analysis, relapse-free success will be the favourable outcome. Unfavourable outcomes include death, failure, lost to follow-up during treatment and relapse (patients withdrawn will be excluded).

Adherence: Adherence will be assessed by the number of patients who are receiving the experimental treatment arm among all eligible patients, compared to the number of patients on the control treatment arm. Patients are considered adherent when 90% of the treatment doses were taken. Adherence is assessed based on the information on the treatment cards, measured over the total treatment period.

*Processing time*: The cumulative delay between sample collection and the start of RR-TB treatment.

*Registration rate:* The number of patients who started treatment among those with confirmed RR-TB.

